**Health technology**

|                |                                                                                                                                                                             |
|----------------|-----------------------------------------------------------------------------------------------------------------------------------------------------------------------------|
| Health economy | 
 
• Cost-effectiveness (i.e., based on length of stay in hospital, advanced care requirement, costs of measurements)
 
 |
|----------------|-----------------------------------------------------------------------------------------------------------------------------------------------------------------------------|

**Exploratory mechanistic endpoints**

|                      |                                                                                                                                                                                                                                                                                                                                                                                                                                                                                                                                                                         |
|----------------------|-------------------------------------------------------------------------------------------------------------------------------------------------------------------------------------------------------------------------------------------------------------------------------------------------------------------------------------------------------------------------------------------------------------------------------------------------------------------------------------------------------------------------------------------------------------------------|
| Hemodynamic endotype | 
 
• Starling SV monitor parameters (e.g. CI, TPRI, SVI) up to three hours after ED arrival
 
• Hemodynamic parameters (e.g. systolic blood pressure, diastolic blood pressure, MAP, heart rate, lactate, CRT) up to three hours after ED arrival
 
• Photoplethysmography waveform characteristics (e.g. systolic and diastolic peak amplitude) during ED stay
 
• Electrocardiography waveform characteristics (e.g. pulse-transit-time and heart rate variability (HRV)-features) during ED stay
 
 |
|----------------------|-------------------------------------------------------------------------------------------------------------------------------------------------------------------------------------------------------------------------------------------------------------------------------------------------------------------------------------------------------------------------------------------------------------------------------------------------------------------------------------------------------------------------------------------------------------------------|

**8.1.3 Other study parameters (if applicable)**

Not applicable.

## 8.2 Randomisation, blinding and treatment allocation

Subjects will be randomized to either the treatment or control arm of the study, ideally at the moment the treating physician decides to admit the patient to the ED. This randomization process begins as soon as the patient is registered for the ED, even before their arrival.

The randomization process at ED arrival will be facilitated by the REDCap randomization module within REDCap electronic data capture tools hosted at the UMCG. Initially, a researcher will identify potential study participants who meet the inclusion criteria based on information provided by the treating physician. Each prospective participant will be assigned a pseudo-anonymized screening ID generated within the REDCap application. This screening ID will encompass both the deferred consent process and the randomization procedure. The randomization will occur through the REDcap module during the screening, determining the assigned treatment arm.

Once the patient arrives and is included in the study, the assigned treatment arm will be communicated to both the research and treatment teams. Any patients that are enrolled but are found to be ineligible based on exclusion criteria will be exited from the study at that point.

Subjects will be randomized in a 1:1 allocation ratio (treatment to control). It is important to note that the randomization process is not blinded in this study. Both the investigator and the physician are aware of the treatment strategy assigned to each subject.

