## 4. STUDY POPULATION

### 4.1 Population (base)

Subjects will be enrolled upon Emergency Department (ED) arrival. Adult patients with confirmed or suspected infection with a need for hemodynamic resuscitation will be considered a candidate for the study. A subject needs to be enrolled within one hour after ED arrival. Once enrolled, subjects will be randomly assigned using the designated randomization procedure. After confirming that the inclusion and exclusion criteria are met, the Starling sensors will be positioned and connected to the Starling SV monitor. To ensure accurate data collection during the study, the readings from the sensors will be validated before initiating the data collection period. To ensure timely intervention in this acute setting, a deferred consent (DC) strategy is employed, facilitated by a proxy if necessary. More information about the DC-procedure is available in 'Chapter 11.2: Recruitment and consent'.

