### 4.2 Inclusion criteria

In order to be eligible to participate in this study, a subject must meet all of the following criteria:

- Adult patients ( $\geq 18$  years of age);
- Referred to internal medicine, nephrology, geriatric medicine, oncology, hematology, lung medicine, rheumatology, gastrointestinal / liver medicine, urology, or emergency medicine (non-trauma);
- Confirmed or suspected infection according to the physician's judgement upon arrival to the ED, based the presence of an acute phase response not due to an alternative non-infectious cause (i.e., body temperature  $< 36^{\circ}\text{C}$  or  $> 38^{\circ}\text{C}$ , leukocyte count  $> 12 \times 10^9/\text{L}$  or C-reactive protein  $> 50 \text{ mg/L}$ ), and/or on symptoms suggestive for an infection (e.g. productive cough, dyspnea, dysuria, pollakisuria, abdominal pain, erythema)
- Need for hemodynamic resuscitation, based on any of the following (*first measurement at ED arrival [triage]*):
  - Mean arterial pressure (MAP)  $< 70 \text{ mmHg}$
  - Systolic blood pressure (SBP)  $< 90 \text{ mmHg}$  or a SBP decrease  $> 40 \text{ mmHg}$
  - Lactate  $> 4.0 \text{ mmol/L}$
  - Shock index\*  $> 0.9$
- Enrolled in study within one hour after ED arrival

\* Shock index is the heart rate divided by the systolic blood pressure, an indicator for the severity of hypovolemic shock.

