### 4.3 Exclusion criteria

A potential subject who meets any of the following criteria will be excluded from participation in this study:

- Primary diagnosis of: acute cerebral vascular event, acute coronary syndrome, acute pulmonary edema, status asthmaticus, major cardiac arrhythmia, drug overdose, or injury from burn or trauma, diabetic ketoacidosis, hyper-osmolality syndrome, pancreatitis
- Known aortic insufficiency, aortic abnormalities, or intraventricular heart defect, such as ventral septal defect or atrial septal defect
- Known advanced heart failure – meaning NYHA IV functional class HF, on waiting list for heart transplant, LVAD recipient or chronic inotrope use.
- Known end-stage kidney disease (dialysis-dependent CKD stage 5 or  $\text{eGFR} < 15 \text{ mL/min/1.73 m}^2$ )
- Decompensated liver cirrhosis at ED admission (e.g., ascites, hepatic encephalopathy, or variceal bleeding)

- Hemodynamic instability due to active bleeding
- Patient has received >1 liter of IV fluid prior to study randomization
- Requires immediate surgery
- Transfer from another hospital after initiation of therapy (a.o. referred by another hospital ICU) or another in-hospital setting
- Pregnant women
- Trauma patients
- Suspected intra-abdominal hypertension, based on the presence of portal hypertension (i.e. presence of ascites due to liver cirrhosis, esophageal varices or as measured by Doppler ultrasound)
- Inability to obtain IV access
- Patient uncouples from treatment algorithm
- Patient should be excluded based on the opinion of the Clinician/Investigator
- Not able to commence treatment protocol within 1 hour after randomization
- Potential ICU-admission unwanted by advanced care directive (e.g., limited life expectancy)

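### Section 8.2 lets the arm be drawn before eligibility is settled and exits patients after enrolment, so concealment is not secured and exits can depend on the arm

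*Protocol*

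**What the plan says.** **Section 8.2, timing of the draw.** "This randomization process begins as soon as the patient is registered for the ED, even before their arrival", and "The randomization will occur through the REDcap module during the screening, determining the assigned treatment arm". The same section also speaks of randomisation taking place at ED arrival.

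**Section 8.2, disclosure.** "Once the patient arrives and is included in the study, the assigned treatment arm will be communicated to both the research and treatment teams". The trial is open: "Both the investigator and the physician are aware of the treatment strategy assigned to each subject".

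**Section 8.2, exits.** "Any patients that are enrolled but are found to be ineligible based on exclusion criteria will be exited from the study at that point".

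**Section 4.2.** Need for resuscitation is judged on blood pressure, lactate or shock index, with the qualifier "first measurement at ED arrival [triage".

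**Section 4.3.** The exclusion list includes "Patient should be excluded based on the opinion of the Clinician/Investigator". Two further items can only be known after the draw: failure to start the treatment protocol within an hour of randomisation, and uncoupling from the treatment algorithm.

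**Section 4.1.** "Once enrolled, subjects will be randomly assigned using the designated randomization procedure". The sentence after it says that the sensors are placed once the inclusion and exclusion criteria have been confirmed.

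**Section 11.2.1 (printed under 10.2).** The patient is recruited, then randomised, then told the result.

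**Section 9.** The ITT set is limited to randomised patients who signed deferred consent and met the eligibility criteria.

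**The concern.** Randomisation supports the comparison only if the decision to keep a patient is made without knowledge of the arm. Section 8.2 allows an arm to exist while a main inclusion criterion has not yet been measured. It then removes patients at or after the point where the arm is disclosed, partly on a discretionary ground. Section 9 drops those patients from the primary analysis. If removal is influenced by the arm, the groups differ by more than chance, and no later analysis can recover the patients who were removed. The exposure is greater here because the trial is open and single-centre, and the primary endpoint, fluid volume over three hours, is decided by clinicians who know the arm.

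**Working it through.** **1. Order of events, section by section.**

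| Section | Order given |
|---|---|
| 8.2 | Registration (possibly before arrival), screening ID, draw during screening, arrival and inclusion, arm communicated, exit if an exclusion criterion is found |
| 4.1 | Enrolment on ED arrival, draw, sensors placed after the criteria are confirmed |
| 11.2.1 | Identification on ED admission, recruitment, draw, patient told the result, treatment |

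These cannot all be followed. Section 4.1 is not a clean counter-text either, because it leaves open whether criteria are confirmed before or after the draw.

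**2. Can eligibility be known at the draw?** Before arrival it cannot, because 4.2 relies on triage values.

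**3. Who could know the arm?** Under 8.2 a researcher screens and the draw is made in REDCap during that screening. Nothing says the result is hidden from this researcher. Under 8.3 the same team assesses the patient and makes recommendations on resuscitation.

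**4. Can exits differ by arm?** The exit sentence follows the disclosure sentence, and one exclusion is a matter of opinion. Uncoupling from the algorithm applies naturally only to the intervention arm, since 5.1 mandates no therapeutic protocol for controls.

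**5. Size, as illustration only.** The protocol has no figure for exits, so there is none to reproduce.
- Inputs from section 4.4: 188/2 = 94 per arm, two-sided alpha 0.05, Welch t-test.
- Assumptions: no true effect, outcome SD 1, exits in one arm only, and correlation ρ between exit propensity and outcome.
- Exit propensity: u = ρ·y + √(1−ρ²)·e, with y the outcome and e independent noise. The k patients with the highest u leave.
- For 5%: 0.05 × 94 = 4.7, so k = 5.

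Expected bias is ρ·k·m/(94−k), where m is the mean of the k largest of 94 standard normal values. For k = 5, m = 1.99:
- ρ = 0.3: 0.3 × 5 × 1.99/89 = 0.034 SD
- ρ = 0.5: 0.5 × 5 × 1.99/89 = 0.056 SD
- ρ = 1: 5 × 1.99/89 = 0.112 SD

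Simulation with 100,000 replicates (bias in SD / type I error):

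| Exits in one arm | ρ = 0 | ρ = 0.3 | ρ = 0.5 | ρ = 1 (extreme) |
|---|---|---|---|---|
| 5% (5 of 94) | 0.00 / 5.0% | 0.03 / 5.7% | 0.06 / 6.8% | 0.11 / 13.5% |
| 10% (9 of 94) | 0.00 / 5.0% | 0.06 / 6.6% | 0.09 / 9.9% | 0.19 / 27.9% |
| 15% (14 of 94) | 0.00 / 5.1% | 0.08 / 8.4% | 0.13 / 15.2% | 0.27 / 50.0% |

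When the same exit rule acts equally in both arms, the mean difference returns to zero. Against the effect size of 0.45 stated in 4.4, the bias at 5% exits is 0.03/0.45 = 7% to 0.06/0.45 = 13% of the design effect at ρ of 0.3 to 0.5.

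**The case against.** The strongest reply is that 8.2 withholds the arm until the patient has arrived and been included, so inclusion comes before disclosure. That is a real, partial safeguard. A reader might infer that concealment is lost outright. The text does not support this: it nowhere says that the screening researcher sees the draw, and the statement that the process is unblinded describes open treatment, not foreknowledge at enrolment. What stands is that the protocol does not say the draw is hidden either, and that the exit rule operates at or after disclosure.

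A second reply is that a pre-arrival draw is only one reading. Section 8.2 says the process begins at registration, and 4.1, 8.3 and 11.2.1 all start on arrival or admission. This is fair, and it is why the order has to be reconciled.

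A third reply is that removing truly ineligible patients does no harm. That holds if removal rests on facts fixed before randomisation and judged blind to arm. The protocol requires neither.

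A reader might also count an assumed share of the 188 as triage failures exited with a known arm. That does not follow. The exit rule concerns exclusion criteria, whereas triage values are inclusion criteria. A patient who fails them is not included, so under 8.2 the arm is not communicated. Also, 188 is the planned number of participants, not of draws.

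**Conclusion.** The concern holds in this form: the protocol gives conflicting orders for enrolment, eligibility and randomisation, does not secure concealment, and permits exits that can depend on the arm and that leave the primary analysis. The contradiction and the missing safeguard are certain from the text. The size of any bias is not, because no exit rate is given. With 5% exits confined to one arm, type I error would be about 6% to 7% at correlations of 0.3 to 0.5. The 13.5% figure needs exits that track three-hour fluid volume perfectly, although that volume is not yet observed at inclusion, so it is a ceiling and not an expectation. Exits unrelated to arm would cause no bias. The case for change rests on the rule as written and does not depend on any of these figures. The sample size is not affected.

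**What to change.** - **Sections 4.1, 8.2 and 11.2.1:** state one order: arrival; triage values entered; every criterion assessable at entry confirmed and locked in REDCap; only then is the arm generated and released. Delete the clause in 8.2 that allows a start before arrival, and say who sees the arm and when.
- **Section 4.3:** move out of the exclusion list the two items that can only occur after randomisation (not starting within an hour of randomisation, and uncoupling from the algorithm). They cannot be confirmed before a draw.
- **Section 9:** redefine the ITT set so that randomised patients stay as allocated as far as deferred consent allows. Section 11.2.1 requires deletion of data when deferred consent is not given, and that limit remains.
- **Exit rule in 8.2:** allow later removal only on facts that predate randomisation, judged blind to arm, and report removals by arm.

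The cost is edits to five sections (4.1, 4.3, 8.2, 9 and 11.2.1) and a REDCap rule that blocks the draw until the eligibility form is locked. The draw comes a few minutes later, within the one-hour enrolment window of 4.2.

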## 8.3 Study procedures

### Screening and enrollment

Patients will be recruited by the FLUIDS research team. First, ED physician and/or nurse will screen all patients entering the ED for potential inclusion in the study, specifically between 9 am and 5 pm during all weekdays. If a patient is eligible for participating in the study, the ED physician/nurse will promptly notify a FLUIDS-researcher present at the ED. Subsequently, this researcher will approach and enrol the eligible patient, being actively involved in the initial assessment and providing recommendations to the attending physician regarding hemodynamic resuscitation.

The FLUIDS research team will consist of fully trained individuals with a medical background and research affinity. Prior to the study start, the research team will undergo comprehensive training on utilizing the Starling SV monitor, interpreting results and conducting PoCUS measurements. Additionally, a follow-up procedure will be established, where the research team is responsible for implementing the Starling SV monitor protocol during subsequent assessments.

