**Intervention:** In the experimental arm, personalized hemodynamic resuscitation will be guided by the Starling SV monitor, with fluid responsiveness assessed during fluid boluses administered based on the increase in stroke volume index as measured by the Starling SV monitor. The control arm will receive standard care determined by the treating physician. All fluids administered will be balanced fluids.

**Main study parameters/endpoints:** The primary end point is the volume (in liters) of IV fluid resuscitation within three hours since ED admission.

**Nature and extent of the burden and risks associated with participation, benefit and group relatedness:** In this intervention study, the utilization of the Starling SV monitor provides significant benefits for sepsis patients in the ED. By tailoring treatment plans to individual hemodynamic changes, patients receive precise fluid administration and timely initiation of vasopressor therapy, reducing the risks of prolonged hypotension and fluid overload. This personalized approach has the potential to optimize sepsis management and improve outcomes. Although there are minimal risks associated with the monitor, such as minimal adverse events and the potential for device malfunction or misinterpretation of readings, proper training, adherence to protocols, and regular evaluation can mitigate these risks and ensure patient safety. Overall, the benefits of the Starling SV monitor outweigh its risks, making it a valuable tool in improving patient outcomes.

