#### Groups

Experimental arm: personalized hemodynamic resuscitation (94 patients)

Patients will receive an IV fluid bolus directly after inclusion. Next, measurement of the stroke volume index change in response to the fluid bolus by the Starling SV will be used to determine fluid responsiveness. Vital parameters and fluid responsiveness will be used to guide hemodynamic resuscitation, consisting of IV fluids and/or vasopressors, during the first 3 hours. See chapter 5 and figure 1 for a detailed description of the study procedures.

Control arm: standard care (94 patients)

Patients will receive an IV fluid bolus directly after inclusion. Vital parameters will be used to guide hemodynamic resuscitation, consisting of IV fluids and/or vasopressors, during the first 3 hours. See chapter 5 for a detailed description of the study procedures.

[figure not shown]

**Figure 1: Flowchart personalized protocol.** Adult patients with confirmed or suspected infection with need for hemodynamic resuscitation, will be included into the study. A dynamic assessment of fluid responsiveness using the Starling SV monitor will be performed at every clinical decision point with concordant treatment (volume or vasopressors). MAP: mean arterial pressure; SBP: systolic blood pressure; NE: noradrenaline; PoCUS: Point-of-Care Ultrasound; L: lactate; SI: shock index\*; CI: cardiac index; PLR: passive leg raise; IV: intravenous; \*shock index is heart rate divided by systolic blood pressure;

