## 5. TREATMENT OF SUBJECTS

### 5.1 Investigational product/treatment

#### Intervention:

The investigational product in this study is the Starling SV monitor, which is a medical device manufactured by Baxter Healthcare. The Starling SV monitor is a non-invasive hemodynamic monitor that provides real-time continuous information about stroke volume index, cardiac index, cardiac output, and total peripheral resistance. In this intervention study, the Starling SV monitor is designed to assist in guiding hemodynamic resuscitation for patients with sepsis.

In the experimental group, patients will receive hemodynamic resuscitation guided by the Starling SV monitor. A dynamic assessment of fluid responsiveness using the monitor will be performed at every clinical decision point during the first three hours of study enrolment.

Vital parameters, including blood pressure and heart rate, are measured upon ED arrival (triage), immediately after administration of a fluid bolus and at least twice per hour during the first 3 hours. Lactate will be measured at ED arrival (triage) and will be repeated every two hours as long as lactate is  $> 4$  mmol/L. Fluid responsiveness will be measured by the Starling SV monitor immediately before and after the administration of fluids. Fluid responsiveness is defined as an increase in stroke volume index by at least 10% after a fluid bolus of 500 mL in 10 min.

First, we will perform the first measurement during the first administration of 500 mL of IV fluids. During both the fluid bolus, we will measure the change in stroke volume index ( $\Delta$ SVI) using the Starling SV and use the stroke volume index change in response to the fluid bolus to determine fluid responsiveness.

If, at any time during the first 3 hours, patients have: (see figure 1)

- MAP  $< 65$  mmHg or systolic blood pressure  $< 90$  mmHg:
  - Fluid responsive (on last measurement): patients will receive (another) 500 mL of IV fluids if considered fluid responsive (and a new Starling SV measurement will be obtained). Reassess after intervention.
  - Not fluid responsive (on last measurement): patients will receive vasopressor (noradrenaline), according to the standard care protocol.\*
- MAP  $\geq 65$  mmHg or systolic blood pressure  $\geq 90$  mmHg combined with SI  $> 0.9$ :

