#### Control:

Vital parameters, including blood pressure and heart rate, are measured upon ED arrival (triage), immediately after administration of a fluid bolus and at least twice per hour during the first 3 hours. Lactate will be measured at ED arrival (triage) and will be repeated every two hours as long as lactate is > 4 mmol/L. No required therapeutic protocol will be mandated for patient treatment, which will be determined at the discretion of the physician and in accordance with hospital standards.

All fluids administered will be balanced fluids. In addition to the fluid resuscitation as described above, all patients will receive a standard 1.5 L per day of IV fluids from the moment of ED arrival. The total volume of IV fluids will be limited to a maximum of 60 ml/kg over three hours to prevent hypervolemia.

The purpose of the control group is to compare the outcomes of hemodynamic resuscitation guided by the Starling SV monitor in the experimental group with the outcomes of standard care in the control group.

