## 8. METHODS

### 8.1 Study parameters/endpoints

#### 8.1.1 Main study parameter/endpoint

The primary end point is the volume (in liters) of IV fluid resuscitation within three hours since ED admission (excluding fluids that are administered pre-hospital)

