#### e. Analysis of potential effect

Not applicable, no medicinal product.

f. Pharmacokinetic considerations

Not applicable, no medicinal product.

g. Study population

The study participants are not healthy volunteers but patients who present to the ED with suspected or confirmed infection and signs of hemodynamic instability. These patients are enrolled during their admission to the emergency department when their condition, although not stable, is not immediately life-threatening. Immediate hemodynamic resuscitation is implemented in both the intervention and control groups, and this does not pose any additional risk for sepsis treatment. The key distinction between the groups lies in the personalized approach to hemodynamic resuscitation.

h. Interaction with other products

Not applicable, no medicinal product.

i. Predictability of effect

Not applicable, no medicinal product.

j. Can effects be managed?

Not applicable, no medicinal product.

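### Section 8.3 lets the enrolling researcher advise the attending physician on resuscitation without limiting that advice to the guided arm, although the advice concerns the decision measured as the primary endpoint

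*Protocol*

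**What the plan says.** **Who advises.** Section 8.3, Screening and enrollment, has ED staff notify a FLUIDS researcher of each eligible patient. That researcher enrols the patient, "being actively involved in the initial assessment and providing recommendations to the attending physician regarding hemodynamic resuscitation". The sentence does not mention an arm.

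**Who knows the arm.** Section 8.2 places randomisation in the screening step. Once the patient has arrived and is included, "the assigned treatment arm will be communicated to both the research and treatment teams". The trial is open.

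**What is measured.** Section 8.1.1: "The primary end point is the volume (in liters) of IV fluid resuscitation within three hours since ED admission", leaving out pre-hospital fluids.

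**What controls should receive.** The Summary says: "The control arm will receive standard care determined by the treating physician". Section 5.1, Control, mandates no therapeutic protocol and refers to treatment "which will be determined at the discretion of the physician and in accordance with hospital standards". Section 3, Groups, says of the control arm: "Vital parameters will be used to guide hemodynamic resuscitation, consisting of IV fluids and/or vasopressors, during the first 3 hours". Section 12.1, item g, adds: "The key distinction between the groups lies in the personalized approach to hemodynamic resuscitation".

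**The concern.** Hemodynamic resuscitation, as section 3 uses the term, means IV fluids and vasopressors. A recommendation on it is therefore a recommendation on the quantity that becomes the primary endpoint. The comparator is supposed to be what the treating physician would do under hospital standards. A trained member of the trial team advising at the bedside is not described as part of those standards.

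Nor is that adviser neutral. Section 1 calls the fixed 30 ml/kg regimen problematic and expects the guided strategy to limit overhydration. Advice to controls that resembles the guided algorithm would pull the arms together. Advice that leans the other way because the arm is known would push them apart. Either would alter the contrast for reasons unrelated to the monitor.

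**Working it through.** The protocol gives no figure on this point, so there is none to reproduce. The check is whether any provision confines the advice to the guided arm, and whether the analysis could remove its effect.

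1. **Does 8.3 limit the advice?** Not in the sentence itself. The next paragraph makes the team responsible for the monitor protocol, but at later assessments. It does not qualify the advice at the initial assessment.

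2. **Does context supply the arm?** Two neighbouring parts of 8.3 also omit the arm. The monitor procedure says that a failed device sends the subject over to the control arm, so a guided-arm patient is meant. The fluid responsiveness procedure points to the personalized flowchart, with the same result. In both, the subject matter belongs to one arm and settles the meaning. Enrolment and initial assessment take place in both arms, so context does not settle it for the advice.

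3. **Do the control-arm provisions exclude advice?** The Summary, section 3 and section 5.1 leave decisions to the physician, vital parameters and hospital standards. None mentions research-team advice. A physician with discretion may receive advice and follow it.

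4. **Can the arm be known when advice is given?** Yes, it can. Section 8.2 discloses it at inclusion. The protocol does not say whether the advice comes before or after that moment.

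5. **Would the analysis remove the effect?** No. The intention-to-treat analysis in section 9 keeps it. The per-protocol set drops major protocol violations, but advice that the protocol permits is not a violation. Table 1 does not list such advice among the data collected.

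**Scale only.** The unit in section 5.1, Intervention, is the response "after a fluid bolus of 500 mL in 10 min". Suppose advice adds or withholds one 500 mL bolus in a share *c* of controls and leaves the guided arm unchanged. Then:

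shift in control mean = 0.5 L × *c*

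| *c* (assumed) | Shift, either direction |
|---|---|
| 10% | 0.5 × 0.10 = 0.05 L |
| 20% | 0.5 × 0.20 = 0.10 L |
| 30% | 0.5 × 0.30 = 0.15 L |

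The share and the use of a 500 mL unit in controls are both assumptions, so the table is not a forecast and the point does not rest on it.

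**The case against.** The best reply is that 8.3 is written around delivering the intervention and habitually leaves out the arm. On that reading the advice is simply the monitor protocol being passed to the physician, and section 5.1 governs controls. Advice at the initial assessment might also be no more than the bolus that section 3 gives both arms after inclusion, which need not shift the contrast. Allocation is openly unblinded, so the physician who decides control fluids already knows the arm.

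Much of this stands. The guided-arm reading is plausible, and shared instructions are harmless. But the text does not confine the advice to either. Staff who follow it literally could advise on control fluids without deviating from the protocol. Open allocation explains why the physician knows the arm; it does not require the trial team to advise on comparator treatment.

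A reader might go further in three ways that the documents do not support:

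- **That 8.3 contradicts the control-arm definition.** It does not. Advice is not binding, and the physician still decides.
- **That the advice is always given with the arm known.** The protocol leaves its timing relative to disclosure open.
- **That a loss of power can be calculated.** The inputs in section 4.4 are fluid balances at 72 hours from a reference trial, not three-hour volumes, and no contamination rate is given. Any such figure would come from assumptions alone.

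**Conclusion.** The point holds as a gap in a conduct rule. Section 8.3 positively assigns an advisory role on resuscitation to trial staff, does not limit it to the guided arm, and allows it to be exercised with allocation known, on the decision that the primary endpoint measures.

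The conclusion rests on the wording of 8.3 and on finding no limiting provision elsewhere in the protocol. It does not assume that the authors intended advice to controls, or that such advice will be given. The size and direction of any bias cannot be derived from the documents. It is best treated as a cheap improvement: if guided-arm-only advice was always meant, the edit merely states it.

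**What to change.** - **Section 8.3, Screening and enrollment:** limit the researcher's recommendations on fluids and vasopressors to the guided arm, after allocation.
- **Section 5.1, Control:** state that the research team only observes, records and conveys the requirements common to both arms (initial bolus, balanced fluids, 1.5 L per day, 60 ml/kg cap). It gives no other fluid or vasopressor advice except for an immediate safety concern, and logs any such advice in REDCap.
- **Starling readings:** do not restrict sensor placement to one arm. Section 4.1 and the exploratory objectives and endpoints name no arm, and a restriction could remove control-arm data meant for them. If readings are taken in controls, conceal them from the treating team during the three hours.

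The cost is a few sentences and an occasional REDCap entry, plus concealment of the readings if controls are monitored. Sample size, endpoints and the physician's freedom to treat are unchanged. The downside is that the researcher must stay out of fluid decisions for controls.
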